**[name]**

**[name]**

**Background and Introduction**

Spinal muscular atrophy (SMA) is an autosomal recessive motor neuron disease characterized by diffuse weakness and muscular atrophy. It is one of the most common neuromuscular conditions, and a leading cause of hereditary infant mortality 1-6. Patients most frequently present in infancy and early childhood, but the clinical spectrum of onset and severity is broad, ranging from the infant with congenital joint contractures and ventilator dependence to adult onset of proximal muscle weakness7. This clinical heterogeneity increases the inherent challenges in clinical trial design for the evaluation of promising new therapies. Our work and that of others have demonstrated that SMA is a progressive motor neuron disease, as reflected by loss of function as well as maximum compound motor action potential amplitudes and motor unit number estimates in a distally innervated hand muscle over time 8. Disease progression can occur rapidly in SMA type 1 infants prior to reaching a stable albeit significantly weak endpoint, while patients with SMA types 2 and 3 often demonstrate a more slowly progressive course, with stable function preserved over many years. As an important prelude to this current proposal, pilot studies at the University of Utah have established stability of functional outcome measures over at least a six month time period in a cohort of non-ambulatory sitters and ambulatory SMA type 2 and 3 children.9

Homozygous deletion of the survival motor neuron 1 (SMN1) gene is found in more than 94% of SMA cases regardless of subtype, and plays a primary role in disease pathogenesis 10-12. The SMN1 gene resides in a duplicated inverted region on chromosome 5q. A near identical copy of the SMN1 gene, designated SMN2, contains a single nucleotide change which alters splicing, and drastically reduces the efficiency by which exon 7 is incorporated, leading to a less than full length mRNA and protein product13. However, SMN2 transcription produces a small percentage of full length SMN protein. An increased number of SMN2 gene copies, with the resulting increase in full-length mRNA levels and protein expression, are associated with a less severe disease phenotype in humans, and phenotypic rescue in an SMN knockout mouse model14-18.

We hypothesize that treatment with VPA increases expression of SMN protein via up-regulation of SMN2 gene expression, resulting in the rescue of motor neurons and allowing re-innervation. Preliminary safety data from a pilot clinical trial at the University of Utah site demonstrates that giving valproic acid without carnitine supplementation is likely to deplete carnitine in a high percentage of SMA patients over the proposed study period, potentially increasing toxicity and resulting in reduced strength and function, thus confounding results of a clinical therapeutic trial. Thus, the trial design takes this into account by examining the use of these two compounds together. A variety of outcome measures will be used to evaluate efficacy of these drugs, including: Blood Chemistries (CBC with platelets, AST, ALT, amylase, lipase, carnitine profile, basic metabolic panel, and valproic acid level); Functional Status/Strength as assessed via Modified Hammersmith Functional Motor Scale (MHFMS) and the Project Cure Functional Motor Scale, Myometry, Pulmonary Function Testing, Quantitative assessment of SMN mRNA from blood samples, Peds QL™ assessment, Max CMAP amplitude/area and Ulnar MUNE (Modified Motor Unit Number Estimation),Growth and vital sign parameters, 3-Day Dietary Record, and Dual Energy X-ray Absorptiometry (DEXA) scanning as a measure of changes in lean muscle mass over time, and investigation of genetic mechanisms which influence the severity of phenotype.

**Objectives**

The primary objective is to assess the safety, tolerability, and efficacy of a combined regimen of oral valproic acid (VPA) and carnitine in SMA patients 2-17 years of age. Secondary objectives are to refine electrophysiological and clinical techniques to help us better follow the course of patients with SMA, particularly as it relates to the primary disease process causing weakness, motor neuron dysfunction and loss. These include: 1) clinical assessments which will help accurately assess functional motor outcomes of patients, 2) electrophysiologic techniques to study and follow the course of motor neuron loss, and 3) investigation of genetic mechanisms which influence the severity of phenotype.

**Patient Selection Criteria**

SMA study patients must meet the following inclusion and exclusion criteria. Family members of eligible study participants will also be included if they choose to donate their blood for genetic testing. They will not participate in any other portion of the study.

***Inclusion Criteria***

*Cohort 1*

1. Confirmed genetic diagnosis of 5q SMA
2. SMA 2 or non-ambulatory SMA 3: SMA 2 subjects must be able to sit independently for at least 3 seconds without support
3. Age 2 to 8 years at time of enrollment

*Cohort 2*

1. Confirmed genetic diagnosis of 5q SMA
2. SMA subjects (SMA types 2 or 3) who can stand independently without braces or other support for up to 2 seconds
3. Age 3 to 17 years at time of study enrollment

***Exclusion Criteria***

*Cohort 1*

1. Modified Hammersmith Functional Motor Scale for children with SMA (MHFMS-SMA) total score < 2 or > 37
2. Need for BiPAP support > 12 hours per day
3. Spinal rod or fixation for scoliosis or anticipated need within six months of enrollment
4. Inability to meet study visit requirements or cooperate reliably with functional testing
5. Transaminases, amylase or lipase > 3.0 x normal values, WBC < 3.0 or neutropenia < 1.0, platelet count < 100 K, or hematocrit < 30 persisting over a 30 day period
6. Coexisting medical conditions that contraindicate travel, testing or study medications
7. Use of medications or supplements which interfere with valproic acid or carnitine metabolism, increase the potential risks of these medications, or are hypothesized to have a beneficial effect in SMA animal models or human neuromuscular disorders within 3 months of study enrollment. Specifically, concomitant use of riluzole, creatine, butyrate derivatives, growth hormone, anabolic steroids, daily albuterol use, anticonvulsants, or other HDAC inhibitors would preclude enrollment.
8. Current use of either VPA or carnitine through participation in another study or been prescribed by their attending physician. If study subject is taking valproic acid or carnitine then patient must be go through a washout period of 12 weeks before been enrolled into the study.
9. Body Mass Index > 90th % for age

*Cohort 2*

1. Spinal rod or fixation for scoliosis or anticipated need within six months of enrollment
2. Inability to meet study visit requirements or cooperate with functional testing
3. Transaminases, amylase or lipase > 3.0 x normal values, WBC < 3.0 or neutropenia < 1.0, platelets < 100 K, or hematocrit < 30 persisting over a 30 day period.
4. Coexisting medical conditions that contraindicate travel, testing or study medications
5. Use of medications or supplements which interfere with valproic acid or carnitine metabolism, increase the potential risks of these medications, or are hypothesized to have a beneficial effect in SMA animal models or human neuromuscular disorders within 3 months of study enrollment. Specifically, concomitant use of riluzole, creatine, butyrate derivatives, growth hormone, anabolic steroids, daily albuterol use, anticonvulsants, or other HDAC inhibitors would preclude enrollment.
6. Current use of either VPA or carnitine through participation in another study or been prescribed by their attending physician. If study subjects is taking valproic acid or carnitine then patient must be go through a washout period of 12 weeks before been enrolled into the study.
7. Body Mass Index > 90th% for age
8. Pregnant women/girls, or those intending to try to become pregnant during the course of the study

**Design**

Implementation of multicenter phase II studies to assess safety, tolerability and efficacy of a combined regimen of oral valproic acid and carnitine will proceed in two parallel studies involving differing SMA cohorts. Preliminary safety data from a pilot clinical trial at the University of Utah site demonstrates that giving valproic acid without carnitine (C) supplementation is likely to deplete carnitine, potentially increasing toxicity and resulting in reduced strength and function, thus confounding results of a clinical therapeutic trial. Cohort 1 trial design is double-blind randomized intention to treat protocol for SMA “sitters”; parallel trial in Cohort 2 SMA “standers and walkers” to explore responsiveness of efficacy outcomes. Cohort 1 will involve SMA subjects with SMA 2 or nonambulatory SMA 3 “sitters”, 2 – 8 years of age. Cohort 2 will involve SMA 2 and 3 subjects: “standers and walkers”, 3 – 17 yrs of age.

**Study procedures**

All study patients from both cohorts will complete two baseline screening visits approximately one month apart. Upon completion of these baseline visits, patients will be divided into treatment arms and be given study medication. Patients in cohort 1 (SMA “sitters”) will be randomized to participate in either the treatment arm (group 1) or the placebo arm (group 2). Patients and investigators will remain blinded for the first six months of the study. After six months, patients in the treatment arm (group 1) will continue on study medication for an additional 6 months. All children enrolled in the placebo arm (group 2) will be switched to study medication and continue on treatment for six months. Thus, half the children will receive treatment for a full 12 months, while the other half will receive treatment for the last 6 months of the study. Patients in cohort 2 (SMA “standers and walkers”) will receive treatment for the entire 12 month time period.

Safety Labs will be drawn 2 – 4 weeks after screening visit 2 to assess safety labs and valproic acid and carnitine levels. This can be done via their local laboratories and the results would be faxed to the central study site. Any dosing adjustments needed will be coordinated through the medical monitor to keep investigators blinded until completion of the study. Additional safety labs for cohort 1 will be drawn 2-4 weeks after Screen 2, 6.5-7 months and 9 months. Additional safety labs for Cohort 2 will be drawn 2-4 weeks after Screen 2. Safety labs do not require a visit to the study site, but may be coordinated through patient’s local pediatrician.

**Cohort 1**: SMA “sitters”: 2 – 8 yrs

|  | Screen 1 | Screen 2 | Safety Lab 1 | Visit 1 | Visit 2 | Safety  Lab 2 | Safety Lab 3 | Visit 3 |
| --- | --- | --- | --- | --- | --- | --- | --- | --- |
|  | T-1 mo | T=0 | .5-1 mos | 3 mos | 6 mos | 6.5-7 mos | 9 mos | 12 mos |
| GROUP 1:  30 subjects | Baseline | Baseline  Start Drugs | VPA+ C | VPA+ C | VPA+C | VPA+C | VPA+C | VPA+C |
| GROUP 2:  30 subjects | Baseline | Baseline | Placebo x2 | Placebo x2 | Placebo x2 | VPA+C | VPA+C | VPA+C |

**Cohort 2:** SMA “standers and walkers”, ages 3 – 17 yrs

|  | Screen 1 | Screen 2 | Safety Lab 1 | Visit 1 | Visit 2 | Safety Lab 2 | Safety Lab 3 | Visit 3 |
| --- | --- | --- | --- | --- | --- | --- | --- | --- |
|  | T-1 mo | T=0 | .5-1 mos | 3 mos | 6 mos | 6.5-7 mos | 9 mos | 12 mos |
| GROUP 3:  30 subjects | Baseline | Baseline  Start Drugs | VPA+ C | VPA+ C | VPA+C | Not Neede | VPA+C | VPA+C |

Clinical testing on the first day of the study visit will include the following: a comprehensive medical history and a general physical examination including tests of blood pressure, breathing rate and oxygen level, heart rate, and measures of growth including height, weight, head circumference, chest circumference, abdominal circumference, and body fat. We estimate this will take about 20 minutes. Nerve conduction testing will be performed at each visit. This testing involves attaching electrodes (½ inch rectangular adhesive pads) over muscles in the hand. The electrodes taped over muscles in the hand will be connected to an EMG machine to record responses. Patients will lay in the position most comfortable for him/her. A nerve will be activated at the wrist and around the elbow by applying brief electrical shocks. Sedation will be necessary in some children, and will be performed under the supervision of the study site investigator, with the assistance of trained nurses to assist with the administration of medications and monitoring patient’s vital signs.  An anesthesiologist or emergency-attending physician will be immediately available should an unexpected complication ensue during the procedure.  Patients will be NPO for several hours prior to the procedure as per routine hospital sedation guidelines.  The goal is conscious sedation, to minimize anxiety and voluntary movement but not to deeply sedate the patient or even put them to sleep and its use will be carefully determined by age and ability to cooperate. Patients will be sedated using Valium 0.5-0.8 mg/kg/dose with a maximum dose of 10 mg by mouth and or Versed 0.1 – 0.3 mg/kg/dose intranasally or by mouth up to 0.5 mg/kg/dose, and may receive up to one dose every ten minutes during the procedure (maximum 2 doses).  Possible complications of the sedation could include respiratory compromise, hypotension or an unexpected paradoxical response to the medication. Heart rate, pulse oximetry, and blood pressure will be measured prior to the start of the study, monitored continuously during the study, and for 30 min following its completion or until the patient is adequately awake and has completely returned to baseline respiratory status. Suction equipment and oxygen will be available at the bedside if needed. The time required for the nerve conduction testing and monitoring is approximately 60 minutes.

Blood samples will be obtained either immediately before or after the nerve conduction testing. If the patient is going to be sedated, the blood draw will be done while the patient is still under sedation. Three to six milliliters of blood is needed at each visit to check for safety monitoring and drug levels. If patients elect to have their DNA collected for genetic studies, an additional five to ten milliliters will be collected during the course of the study. If a DEXA scan is to be completed during this visit, it will occur either immediately before or immediately after the MUNE procedure. The total time of testing on the first day, including all of the testing above, is approximately 2 hours.

Prior to the patient’s arrival for each study visit they will be given a 3 day dietary/supplement record, which they will asked to complete and bring with them. This information will be reviewed with them by a dietician either on their arrival or on the first day of testing. If patients forget to bring their completed dietary record, they will be asked to complete it the following week and return it promptly. The site coordinator will administer the parent questionnaire of the quality of life tool (PedQLTM), which must be filled out by the same parent at each visit. Total time to complete the questionnaires is about 15 minutes.

Clinical testing on the second day includes the following: A physical therapist will perform a functional assessment using either the Modified Hammersmith Functional Motor Scale – SMA (cohort 1) and the Project Cure Functional Motor Scale for SMA (cohort 2). Functional testing will last between 15 to 30 minutes. Patients 5 years of age or older will receive pulmonary function testing and myometry testing. A physical therapist will perform myometry testing which uses a small device to help measure strength of patients’ hand grip and arm flexion and leg extension. A technician will perform pulmonary function testing which includes routine spiromerty, maximum inspiratory pressure (MIP) and maximum expiratory pressure (MEP). This testing will take approximately 30 minutes. Patients 5 years or older will complete the age appropriate questionnaire of the quality of life tool PedQLTM on this day.

Participation in this study will include 5 visits and 7 total blood tests over a 13 month period. Each visit will be two to three days long. The first day will be for travel if needed, the second day will include clinical exam, nerve conduction testing and collection of blood samples, and all functional testing will be performed on the third day. Follow-up Study Visits after beginning therapy will be at 3 months (Visit 1), 6 months (Visit 2) and 12 months (Visit 3) when the patient will stop drug. All evaluations will be performed at each follow-up visit. To account for scheduling conflicts, illnesses, or family emergencies, study visits may occur within a four week window (plus or minus 2 weeks) from the anticipated date.

The following table illustrates the study procedure outline:

|  | Screening | | Visit | | | | | |
| --- | --- | --- | --- | --- | --- | --- | --- | --- |
|  | 1 | 2 | Safety Lab 1 | 1 | 2 | Safety Lab 2 | Safety Lab 3 | 3 |
| Time - from start of drug | - 4 wks | Start | Month .5 - 1 | Month 3 | Month 6 | Month* 6.5 - 7 | Month 9 | Month 12 |
| Physical Examination and Vital signs | X | X |  | X | X |  |  | X |
| Growth Parameters | X | X |  | X | X |  |  | X |
| Blood Draw | X | X | X | X | X | X | X | X |
| Quality of Life Survey: PEDS QLTM  Parent version: all  Child versions: > 5 yrs | X | X |  | X | X |  |  | X |
| Nerve Conduction Testing | X | X |  | X | X |  |  | X |
| Functional Testing | X | X |  | X | X |  |  | X |
| 3 day dietary, supplements, medication survey | X | X |  | X | X |  |  | X |
| DEXA Scan** |  | X |  |  | X |  |  | X |
| Start Drug |  | X |  |  | X |  |  |  |
| Stop Drug |  |  |  |  |  |  |  | X |

*Safety Lab 2 will be done approximately at month 6.5-7, but must be scheduled to occur 2 weeks to 1 month after v2, even if V2 is not held in the window of month 6 +/- 2 weeks.

**DEXA scans apply to Cohort 1 only

VPA and placebo will be acquired from the pharmaceutical company Abbott Pharmaceutical and carnitine and placebo from Sigma-Tau Pharmaceutical. Study medications and placebos will be sent to the central pharmacy at Primary Children’s Medical Center for direct dispensing to study patients. At screening visit 2, when inclusion criteria are fulfilled, the central pharmacist will be notified to prepare a 90 day supply (+ 14 day emergency supply) and ship to study patient. At Study visit 1 (3 month follow-up), another 90 day supply will be requested by the study site investigator and distributed by the central pharmacy. Patients will receive enough extra study medication to maintain a 14 day emergency supply. At study visit 2 (6 month follow-up), a 180 day supply similarly be supplied to take the patient to Study visit 3 (12 month follow-up). At Study visit 3, study medications will be discontinued.

Dosage initiation of VPA will start at 10-20mg/kg/day divided into two or three doses. After 2 week follow-up safety lab the dose will be increased to achieve a therapeutic trough level 50-120 micrograms/ml. All subjects will receive VPA in the form of 125 mg sprinkle capsules. Dosage for Carnitor will be 50 mg/kg/day with a maximum dose of 1000 mg/day divided into two doses. Carnitor elixir comes as 500 mg/5 ml. All subjects will be given Carnitor or equivalent placebo in the liquid form. At each follow-up visit, the caregiver will be asked to present a log of drug administration and to return all unused capsules. The log and returned drug will be reviewed by the Site Coordinator and results tabulated.

While genetic confirmation of 5q SMA is necessary for inclusion in this study, that information will come from the routine clinical evaluation of patients prior to enrollment. New genetic information obtained in our study will include the SMN2 copy number, a known modifier of SMA phenotype, which will be performed in the CLIA certified laboratory of [name] at Ohio State University. Blood will also be collected for mRNA studies which will be performed at Montreal in the laboratory of [name] and for protein studies to be conducted at the University of Utah. We will also request consent to establish a DNA and cell line resource on each patient and their parents, so as to have this resource available to perform further genetic studies which might distinguish “responders” from “non-responders”. However, patients and parents may refuse to participate in the development of a permanent DNA and cell line database without affecting their eligibility for enrollment in this study.

**Standard of Care vs. Research-Related Procedures**: There are no standard-of-care procedures in this

study; every procedure is strictly research related. Although this study hopes to contribute to a future

standard-of-care treatment plan for SMA, as of this date no treatment has yet been approved.

**Data Safety and Monitoring:** The University of Utah General Clinical Research Center (GCRC)

Informatics Core serves as the infrastructure for a data coordinating center (DCC). The GCRC Informatics

Core is responsible for applying the best practices of data management, study design, safety reporting and

clinical trial conduct to clinical research protocols. It will also provide project direction and management,

data security and other necessary support from existing resources within the GCRC Informatics Core. There will be additional staff required for this project, a part time Database Administrator (DBA) and clinic coordinator.

The data management system is based on the Clinical Research Information System (CRIS) version 4 that has been developed, tested and implemented at the University of Utah since October 2003. Its implementation was based on a clinical study process model developed in 1999.

The DSM committee consist of 6 members who are completely independent of all investigators and have no financial, scientific or other conflict of interest with the study. A quorum is 4 voting members. The Principal Investigator and Data Management Biostatistician are non-voting members.

[name] [name] Medical Monitor/Pediatric Neurologist

[name], Ph.D Biostatistician

[name] Ethicist

[name], PT Pediatric Physical Therapist

[name], PhD Biochemical Geneticist

[name], PhD Clinical Neonatologist/Pharmacologist

Criteria for discontinuation of the study have been set by the Data Safety Monitoring Committee, in consultation with the Principal Investigator.

Patients are made aware of all potential risks during the informed consent process. Safety assessments consist of monitoring and recording all adverse events and serious adverse events and the regular monitoring of parameters including hematology, liver function tests, vital signs, and general physical condition. Blood draws will be obtained during each study visit and between some study visits to monitor safety levels.

The Medical Monitor (MM) reviews all laboratory data within a week of each visit and on an as-needed basis to determine whether any subject suffers evidence of organ damage or an adverse event and to make decisions regarding dosage adjustments. All lab results are provided on laboratory reports along with normal limits for each value. The MM notes any abnormalities and signs the case report form before returning to the Clinical Trials Manager. In addition, the MM receives monthly reports summarizing any adverse events.

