Secondary endpoints include an evaluation of the change in MHFMA-SMA at 12 months. We will evaluate the change from second baseline to 12 months and compare both groups. This will be done using a t-test. Since all patients will cross over to VPA+C at six months, this evaluation will be exploratory to determine whether or not additional treatment time of 12 vs 6 months leads to additional functional benefit in the treatment cohort compared to the placebo cohort and compared to their baseline values. We will also look at the change in MHFMA-SMA from 6 to 12 months for both groups. In addition, generalized estimating equations will be used to incorporate all longitudinal measurements from the second baseline through 12 months to determine if there is a sustainable treatment effect. Additional secondary endpoints include: Pulmonary Function Testing in subjects over five years of age, quantitative SMN mRNA, Peds QL™, CMAP amplitude/area, and MUNE. These endpoints will be exploratory in nature. Some will be hypothesis generating, while others will be confirmatory for the MHFMA-SMA results.

*The analyses of the cohort arm will be as follows:*

The assumption of normality of the change scores will be checked, if it holds then a large-sample z-statistic confidence interval around the mean will be constructed. Change from baseline will be examined and reported with 95% confidence intervals. Gender and age may affect scores; as such a linear regression analysis that includes gender and age will be performed to determine their influence. Subjects that drop out prior to six months will be excluded from the primary analysis. If the subjects had a 3-month evaluation then an additional analysis will be performed using the last observation carried forward approach to determine the effect on the outcome of subjects with missing data.

Additional secondary endpoints include: Pulmonary Function Testing in subjects over five years of age, Quantitative assessment of SMN mRNA, Peds QL™, Maximum CMAP amplitude/area: ulnar nerve /hypothenar eminence, Ulnar MUNE, growth and vital sign parameters, dietary assessment. These endpoints will be examined at each time point with means and confidence intervals as well as an analysis over time. These exploratory analyses will aid in the design of follow-up studies in this cohort of patients.

*Randomization*

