Randomization will be performed using a permuted block design balancing for institution. Each institution must submit a Study Agent Shipment Form as soon as the individual responsible for the study agent has been identified and the site has institutional IRB approval for the study. The Shipment Form must be submitted to the Central Pharmacy in order to receive drug shipment with adequate processing time before calling to register the first case. Patients can be registered only after pretreatment evaluation is completed and eligibility criteria are met. Patients are registered prior to the start of any protocol therapy by calling the Statistical Office at Children’s Hospital of Philadelphia [contact], Monday through Friday, 8:30 a.m. to 5:00 p.m. ET. This process will be performed following screening visit 1 and verification by the lead Investigator at each study site that the subject meets all inclusion/exclusion criteria. The patient will be randomized/registered and a case number will be assigned and confirmed by email. After each randomization/registration, the Statistical Office will provide the double-blinded treatment assignment to the Central Pharmacy, who will ship the assigned therapy by next day shipment (Priority Overnight) to the institution. NOTE: Sites must plan ahead due to the following shipping schedule: Study agent/placebo for patients randomized after 4 p.m. ET will be shipped the following business day. Study agent/placebo will be shipped to U.S. sites Monday to Thursday only. Study agent/placebo will be shipped to Canadian sites Monday to Wednesday only. For example, study agent/placebo for a patient randomized to a U.S. site on Thursday after 4 p.m. will be shipped on the following Monday (or Tuesday, if Monday is a holiday). Study agent/placebo will not be shipped on holidays or December 23rd through January 2nd. Each institution is responsible for notifying the Central Pharmacy if study agent/placebo does not arrive on the expected date.

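### A forgotten 3-day diet record is completed in the week after the visit, so at visits where drug starts, switches or stops it can describe the wrong treatment state (minor; exploratory data only)

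*Protocol*

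**What the plan says.** Protocol, Study procedures, sets the normal timing: "Prior to the patient’s arrival for each study visit they will be given a 3 day dietary/supplement record", to be filled in and brought along, with a dietician going through it on arrival or on the first test day. The record is thus meant to describe the days before the visit. The next rule covers the family that comes without it: "If patients forget to bring their completed dietary record, they will be asked to complete it the following week and return it promptly".

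The procedure table in the same section schedules the "3 day dietary, supplements, medication survey" at Screen 1, Screen 2, Visit 1 (month 3), Visit 2 (month 6) and Visit 3 (month 12).

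Three of these visits are also treatment change points for some or all children:
- **Screen 2.** The table marks drug start here, and the supply is triggered here: "At screening visit 2, when inclusion criteria are fulfilled, the central pharmacist will be notified to prepare a 90 day supply".
- **Visit 2.** "All children enrolled in the placebo arm (group 2) will be switched to study medication and continue on treatment for six months". Group 1 and Cohort 2 simply continue.
- **Visit 3.** "At Study visit 3, study medications will be discontinued".

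The 3-day record is named among the outcome measures in Background and Introduction. Under Statistical Analysis, Data Analysis and Interpretation, the Cohort 2 secondary endpoints include "growth and vital sign parameters, dietary assessment". They are to be summarised at each time point and over time, and are called exploratory.

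**The concern.** A record meant to look back from the visit becomes, when forgotten, a record that looks forward from it. Where treatment is the same on both sides of the visit this hardly matters. Where the visit is the boundary between two treatment states, the value is filed under a state it may not describe. A Screen 2 baseline may be partly on drug, an end-of-placebo record in Group 2 may be on VPA plus carnitine, and a month-12 record is off drug.

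A site that follows the rule exactly produces this. Nothing in the Protocol asks for recall of the pre-visit days, has the dates covered written down, or sets late records apart.

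Cohort 2 has the most at stake. It has one arm, so change from baseline is the only treatment contrast for diet, and that contrast depends on the baseline being before drug. A lesser point is that the same form is the scheduled survey of supplements and medication. A late Visit 2 record in Group 2 may therefore miss the end of the placebo phase.

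**Working it through.** The plan gives no figure on this point, so there is nothing to reproduce. The check sets the five record dates against the treatment change points, then expresses the effect on a baseline change.

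**Step 1. Which records are exposed.** Inputs, all from Study procedures: five records per child, 30 children in each of Groups 1, 2 and 3 (Group 3 is Cohort 2), and the start, switch and stop visits listed above. The entries show whether active treatment differs between the days before and the week after the visit.

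| Record | Group 1 | Group 2 | Cohort 2 |
| --- | --- | --- | --- |
| Screen 1 | no (off drug) | no (off drug) | no (off drug) |
| Screen 2 | may differ (drug start) | no active drug (placebo start) | may differ (drug start) |
| Visit 1 | no | no | no |
| Visit 2 | no | may differ (switch) | no |
| Visit 3 | yes (stop) | yes (stop) | yes (stop) |

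Each group has 2 exposed records of 5. Over the trial:
- scheduled records: 90 × 5 = 450
- exposed records: 60 (Screen 2, Group 1 and Cohort 2) + 30 (Visit 2, Group 2) + 90 (Visit 3) = 180
- 180 / 450 = 40%

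This is the share at risk if forgotten. It is not a predicted error rate, because the Protocol gives no rate of forgotten records.

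**Step 2. Effect on change from the Screen 2 baseline.** Let μ be mean intake off drug and D the true mean change on treatment. Let p be the share of Screen 2 records completed late, and f the fraction of D already present in the week after Screen 2. Assume that lateness is unrelated to intake.

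- Mean recorded at Screen 2 = (1 − p)μ + p(μ + fD) = μ + pfD
- Mean recorded later on treatment = μ + D
- Apparent change = D − pfD = D(1 − pf)

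The attenuation is therefore p × f. Both inputs are assumptions:

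| | f = 0.25 | f = 0.5 | f = 1 |
| --- | --- | --- | --- |
| p = 5% | 1.25% | 2.5% | 5% |
| p = 20% | 5% | 10% | 20% |

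**Step 3. Visit 3.** By the same reasoning, if a share q of Visit 3 records is late and a fraction g of the effect is lost within a week of stopping, the 12-month change loses a further q × g. The Protocol gives neither quantity.

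**The case against.** Several points on the other side stand and set the limits of this one.

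- **Reach in Cohort 2.** Because Screen 2, Visit 2 and Visit 3 are all change points somewhere in the trial, a reader might infer that three of the five records behind the dietary endpoint are exposed. They are not. Cohort 2 stays on treatment throughout, so its Visit 2 record is unaffected and the count is two. The Visit 2 problem belongs to Group 2 of Cohort 1. Diet is not listed among the Cohort 1 secondary endpoints, and no placebo comparison of it is planned.
- **Late does not always mean on drug.** A reader might infer that every late Screen 2 record is an on-drug record. Group 2 starts placebo there. For the others the first-dose date is not firmly fixed. The Randomization subsection places registration after Screen 1 and names the Central Pharmacy, "who will ship the assigned therapy by next day shipment (Priority Overnight) to the institution", on certain weekdays only. Study procedures and Control of Investigational Devices/Drugs have supply sent to the patient or parents. Part of the following week may still be off drug.
- **Early effect.** VPA begins at a starting dose and is raised after the two-week safety lab, so a week-1 record need not show a full effect. A 20% attenuation is thus the top of the range, reached only if 20% of records are late and the whole effect appears within days.
- **An untreated record remains.** Screen 1 comes about four weeks before drug, and even a late Screen 1 record is off drug.
- **Supplements and medication.** A medical history is also taken at study visits, so the form is not the only chance to ask about month-6 use.
- **Wording.** The rule could mean finishing a form already begun. The plainer reading is a form filled in during the next week, and the ambiguity itself deserves removal.
- **Delegation.** Excluding late records from a summary could sit in a SAP that is not at hand. The timing rule, however, is fixed in the Protocol, and if the dates covered are not collected, no later analysis can identify the affected records.

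**Conclusion.** The point holds as a minor one. The Protocol's own fallback can place a record on the wrong side of a treatment change. In Cohort 2 this concerns Screen 2 (possibly) and Visit 3. In Cohort 1 it concerns Screen 2 in Group 1, Visit 2 in Group 2, and Visit 3 in both groups. Only forgotten records are affected.

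For change from the Screen 2 baseline the attenuation is p × f, about 1% to 20% over the assumed ranges. It would be smaller still if first doses are delayed by shipping or if Screen 1 is used as baseline. The result rests on the plain reading of the rule and on assumed values of p and f.

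A reader might go further and infer that the efficacy result or the placebo comparison is compromised. The documents do not support that. The primary analysis uses the Modified Hammersmith scale, which is scored at the visit, and the dietary analyses are exploratory.

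**What to change.** Amend the fallback rule in Study procedures and add a field for the dates that each form covers.

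1. Record the calendar dates covered by every 3-day form.
2. Do not use a form covering days after a start, switch or stop of study drug as that visit's value. Keep it, flagged.
3. In its place use the dietician's recall of the three days before the visit, taken at the visit when the form is found missing. For baseline, the Screen 1 record may be used instead.

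The rule can stay as it is where treatment does not change: Screen 1, Visit 1, and Visit 2 in Group 1 and Cohort 2. If staff are to stay blind to arm at Visit 2, apply the replacement to all Cohort 1 children at that visit.

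The cost is a sentence or two and a date field, using a dietician contact that is already planned. The downside is that recall is less exact than a record kept on the day, and a few visit values may be missing. No dose, visit or clinical rule changes.
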